### Fund and contract dissemination strategy focused on adoption

Fund and contract dissemination strategies typically include a request for applications (RFA) to deliver an evidence-based intervention, contracting to ensure understanding of what delivery will entail, and some sort of funding to improve local motivation to adopt the given intervention [6]. As part of this trial, the fund and contract dissemination strategy is used to identify communities with strong cross-organization partnerships and a priority to address childhood obesity locally. Table 2 includes a full specification of this strategy and the HEI trial includes 2 phases—a call for letters of intent (LOI) and an invitation for full proposals based on LOI review. Both processes are developed by the research team and reviewed and revised in partnership with the community advisory board (BHF-CAB). The call for LOIs focuses on describing the attributes of the BHF Online Training Resources and Program Package (i.e., relative advantage, compatibility, complexity, observability, and trialability [25]). The call also highlights financial resources available for the community and the need for a horizontal (i.e., across community organizations) and vertical (i.e., decision makers and doers) systems-based approach to BHF implementation. The target of the fund and contract strategy was to increase community adoption of BHF [23].

### Developing packaged implementation blueprint: BHF Online Training Resources and Program Package focused on adoption and implementation fidelity

A detailed description of the BHF Online Training Resources and Program Package has been published previously [5]. In brief, the package was designed for BHF community facilitators to provide all of the training and materials necessary for program implementation. Specific training modules were developed for a program facilitator and for facilitators of the specific content areas (nutrition, physical activity, and lifestyle). Introductory modules also focused on program initiation and methods to improve program reach. Modules included presentation materials, handouts, lesson plans, facilitator knowledge checks, and self-assessed implementation fidelity checklists. To allow the program facilitator to track family progress and implementation fidelity a data portal was included in the package. The primary target of the BHF Online Training Resources and Program Package was to increase implementation fidelity (operationalized as adherence to protocol and increased facilitator capacity) while allowing adaptability of delivery within and across core intervention elements [26]. This strategy has secondary targets of improved adoption through reducing implementation complexity and improved reach.

### Building Health Families Action Learning Collaborative (BHF-LC) to improve implementation quality

The BHF-LC represents the primary independent variable for the HEI trial whereby 2 to 4 communities receive only the BHF Online Training Resources and Program Package (package only, BHF-PO) and 2 to 4 communities will receive the package and participate in a LC (BHF-LC). The intent of a LC is to bring together community teams with members from different organizations and professional roles (e.g., staff, supervisors, senior leaders) to work together to learn BHF and sustain its use over time. Activities used in the LC model include pre-work activities to build capacity, in-person trainings, and implementation periods between trainings that involve ongoing consultation and quality improvement strategies [6]. Specifically, the BHF-LC includes collaborative learning sessions followed by action periods over a 2-year implementation period. The learning session topics align with the timing of BHF program activities with an early focus on reach and recruitment, followed by a focus on implementation quality, followed by a focus on maintenance of community program implementation. Consultee-centered training [27] is embedded within learning sessions to improve facilitator implementation capacity. This includes instruction on core content, review of BHF implementation data, facilitator reflection on implementation processes, goal setting and feedback relative to implementation outcomes, and group-based problem-solving to improve reach, implementation fidelity, and sustainability. Finally, sustainability action planning will be included in the BHF-LC and focus on strategies to embed program implementation within organization workflows and job responsibilities. The sustainability action planning will also include engaging local payers and public health organizations to explore opportunities for ongoing funding and reimbursement for implementation.

### Evidence-based pediatric weight management intervention

BHF is a 12-month parent-child dyad PWMI program, adapted from Epstein and colleagues’ efficacious traffic light diet (TLD) PWMI, and was tailored to fit rural/micropolitan communities [20, 21]. The BHF program includes a minimum of 32 contact hours consisting of three main program components: nutrition education, behavior modification, and physical activity. Education is provided to children and parents together and independently based on the topic and depth of information [20, 21]. Participants and parents are expected to attend 12 continuous weeks of education (2 h/session) followed by 12 weeks of relapse prevention refresher courses (1 h per session for every 3 weeks). One additional refresher session (2 h) is conducted between 6 months and 1 year to revisit the TLD eating plan and environmental changes, re-ignite social support within the group, and finish with a fun activity. Two follow-up check-in sessions are conducted at 6 and 12 months for approximately 1 h per session.

### Eligibility, recruitment, and allocation

#### Community level

Applying the community engagement approach, the research team and the BHF-CAB disseminated the RFA within and outside their organizations and networks (i.e., applying network weaving strategy) and documented that communities across all 93 counties received the RFA. Eight communities with broad geographic distribution responded to the RFA of which seven rural communities in Nebraska completed a full proposal and were selected as the participating communities for the HEI trial. We then ranked the seven applications in a descending order and allocated the odd-numbered rankings to the (BHF-LC) and the even-numbered rankings to the package-only (BHF-PO) condition [23]. This exercise resulted in four communities in the BHF-LC condition and three communities in the BHF-PO condition. All communities that implement the PWMI will have access to the BHF Online Training Resources and Program Package that includes all of the materials necessary to implement and evaluate the BHF intervention.

Communities assigned to the BHF-PO condition are required to complete a memorandum of agreement (i.e., obtaining formal commitment strategy) to report on the implementation of the PWMI and to use pragmatic evaluation strategies for reach and effectiveness outcomes and to provide de-identified program data for baseline, 6, and 12 months. These communities will also have technical support as needed related to package function, but no other facilitation. Communities allocated to the BHF-LC condition will participate in LC training lessons with additional embedded implementation support activities with a goal to (1) develop local strategies to screen and engage families through the BMI Reporter in schools or clinical screening and referral, (2) increase implementation fidelity, and (3) plan for sustainability.

#### Individual level

Recruitment will be completed by selected communities through school BMI report cards, physician referral, local advertisements, and through word-of-mouth based on locally available resources and guided by the BHF Online Training Resources and Program Package. All materials are designed for local adaptation based on location, time of the session, clinical and school partners, and form of recruitment used. For BHF participation, families will be eligible if they have a 6- to 12-year-old child with a BMI percentile ranking at or above the 95th percentile. Children with major cognitive or physical impairments, parents or children with a contraindication for physical activity and families participating in a concurrent PWMI will be excluded. According to our previous studies [20–22], 8–12 families per cohort would be ideal with a minimum of 5 families and a maximum of 12 families in each cohort. The study goal is to enroll 12 families (*n*=30–48 individuals) per cohort and 2 cohorts per community. With a total of 7 communities recruited, the total PWMI intervention participants are approximately 420–672 parent-child dyads.

### Overview of economic evaluation

This protocol has been reported in line with the Consolidated Health Economic Evaluation Reporting Standards (CHEERS) checklist [28] (see Supplementary File 1: CHEERS Checklist).

The economic evaluation of the HEI trial is two-fold. First is to conduct a cost and cost-effectiveness analysis of the fund and contract dissemination strategy for the BHF adoption, the BHF Online Training Resources and Program Package relative to BHF adoption and implementation, and the BHF-LC implementation strategy for promoting BHF adoption, implementation fidelity, and sustainability for the duration of the trial (12 months). The second is to conduct a cost and cost-effectiveness analysis of the BHF intervention. The CEA will be conducted from an implementing community [29] and limited societal perspective (i.e., including only productivity loss of participants due to the participation in the BHF program). The perspective of implementing community would include costs of time spent on planning, training, recruitment, delivering, and post-session follow-up, resources used, communication with the research team and BHF participants, and opportunity costs of community facilitators. Moreover, we will include the time and costs of the research team for providing training, facilitation, and technical assistance. Costs associated with research administration, data collection, and trial outcome assessment will be excluded. All costs will be categorized as labor and non-labor costs (e.g., space, supplies, or information technology) and expressed as US $2022. The unit of analysis for the economic evaluation is the 7 communities consisting of approximately 21–28 community facilitators who will be provided with BHF Online Training Resources and Program Package with or without a LC implementation strategy to implement and deliver the BHF intervention. The time horizon of the within-trial CEA will be across a 15-month period of time (first 3 months for preparation, and later 12 months for BHF intervention), to incorporate sufficient time to complete the whole implementation process of one BHF cohort, initiating from preparation, training, recruitment, and program delivery to post-intervention follow-up. This differs from the primary clinical effectiveness time horizon of 6 months. Costs and benefits will not be discounted due to a short duration.

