**R**each	-LC- consultee-centered training focusing on recruitment at schools and clinics -Develop a packaged implementation blueprint- referral process	-LC training and consultation sessions -BHF recruitment training -Recruitment activities	-BHF recruitment training -Recruitment activities	-Number, proportion, & representativeness of eligible families screened	C_LC_-C_PO_/E_LC_-E_PO_	Cost of per additional person recruited
**E**ffectiveness	-BHF program training and delivery	-All LC activities -BHF program training and delivery	-BHF program training and delivery	-Reduction in BMI *z*-scores	C_LC_-C_PO_/E_LC_-E_PO_	Cost per additional BMI *z*-score reduced
**A**doption	-Fund and contract	-Response to RFA from potential community stakeholders and organizations	-Response to RFA from potential community stakeholders and organizations	-Objective count of communities responding to RFA and contracted to implement BHF	C_all_/E_all_	Cost per community adoption
	-LC- consultee-centered training with focus on BHF cohort adoption -Develop a packaged implementation blueprint- BHF online training resources & package	-LC training and consultation sessions -Online training and program packaging -BHF program training and delivery	-Online training and program packaging -BHF program training and delivery	-Objective count of # of BHF cohorts initiated	C_LC_-C_PO_/E_LC_-E_PO_	Cost per additional cohort initiated
**I**mplementation	-LC- consultee-centered training with focus on implementation fidelity	-LC training and consultation sessions	None	-Average fidelity scores from the direct observation	C_LC_/E_LC_-E_PO_	Cost per additional changes in fidelity scores
	-Develop a packaged implementation blueprint- BHF online training resources & package	-Online training and program packaging	-Online training and program packaging	-Average knowledge check scores from BHF online training resources -Summarized implementation fidelity assessed via direct observation.	C_all_/E_all_	Cost per knowledge score/unit of implementation fidelity
**M**aintenance- setting level	-LC- sustainability action planning	-LC training and consultation sessions	None	-Objective count of BHF cohort continued	C_LC_/E_LC_-E_PO_	Cost per additional 3rd cohort initiated

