	**Implementation** -Observed adherence to protocol and family engagement at each BHF session -Instructor self-reported fidelity at each BHF session	-Create learning session materials -Delivery learning sessions -Provide individual/group consultation -Conduct knowledge/fidelity checklist -Provide feedback at each learning session -Complete pragmatic evaluations	-Research team -Research team -Research team -Research team -Research team -Research team	BHF-LC	Mid-late	Frequency of the training sessions focusing on implementation	Duration of the sessions
	**Maintenance** -Survey/checklist at 12 months -Objective count of sustained implementation of cohorts in the year following completion of the LC intervention	-Develop sustainability needs assessment checklists -Develop funding matrix development tools -Develop key partner identification and engagement -Develop an ongoing assessment & feedback -Conduct sustainability needs assessment -Examine current and future resources, payer and payment models -Integrate into regular learning meetings & action periods	-Research team & CAB -Research team -Research team -Research team & CAB -Research team -Research team & CAB -Research team	BHF-LC	Late	Frequency of activities/events focusing on maintenance	Duration of the activities

*BHF* Building Healthy Families, *LC* learning collaborative, *PO* Package only, *CAB* community advisory board, *LOI* Letter of intent

^a^Costs are divided among RE-AIM (reach, effectiveness, adoption, implementation, and maintenance) outcomes and are estimated with actions/activities specified for that specific outcome

^b^Costs are divided among implementation outcomes associated with the strategy, based on the activities specified in the action column

^c^Preparation time and travel time (if any) and post-session follow-up (e.g., summary note) are also included

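### The stated 15-month horizon ends before the 2-year learning collaborative does, so the maintenance ICER has no observable outcome within it

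*Protocol article*

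**What the plan says.** All references are to the protocol article.

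- **Horizon.** Overview of economic evaluation states: "The time horizon of the within-trial CEA will be across a 15-month period of time". It is made up of "first 3 months for preparation, and later 12 months for BHF intervention", and the stated reason is "to incorporate sufficient time to complete the whole implementation process of one BHF cohort".
- **A second duration.** Earlier in the same section, the evaluation of the LC, sustainability included, is set "for the duration of the trial (12 months". The Methods part of the Abstract also gives 12 months.
- **LC length.** The section on the BHF-LC describes "collaborative learning sessions followed by action periods over a 2-year implementation period", with maintenance as the last topic in the sequence.
- **Maintenance outcome.** Table 2 (under Study design) defines it as "Objective count of sustained implementation of cohorts in the year following completion of the LC intervention". Effect measurement likewise times it after the LC sessions are complete.
- **Maintenance ratio.** Table 1 divides LC cost by the difference between arms and reads the result as "Cost per additional 3rd cohort initiated". The Individual level section plans 2 cohorts per community, so a third lies beyond the planned programme.
- **Discounting.** "Costs and benefits will not be discounted due to a short duration".

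No section gives the maintenance analysis a horizon of its own.

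**The concern.** The horizon was chosen to hold one cohort from preparation to follow-up, and for that purpose it is adequate. The maintenance ratio is a different kind of quantity: its outcome exists only after the LC has finished. If the LC lasts 2 years, the outcome falls entirely after the window closes.

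Sustainability is listed in the primary aim under Study design and is a named target of the economic evaluation. An analyst who follows the stated horizon cannot produce this ratio. One who takes the count later must decide, without guidance, whether LC costs stop at month 15 or run to the end of the LC. Table 2 places sustainability planning at the late stage, so a cut at month 15 probably removes part of the cost of the very strategy being priced. Adopting communities could then see a cost per sustained cohort that leaves out some of the work done to sustain it.

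**Working it through.** **Inputs**
- Horizon H: 15 months, or 12 months on the other statement (Overview of economic evaluation; Abstract).
- LC length L: 24 months (BHF-LC section); 12 months as a sensitivity reading.
- Maintenance window: the 12 months after the LC ends (Table 2).
- LC start s: not stated. Assumed to be month 0 or month 3 (after preparation).

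**The plan's own figure.** 3 + 12 = 15 months, which reproduces.

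**Formulas**
- LC end = s + L
- Share of LC time covered = (min(H, s + L) − s) / L
- Post-LC months observed = max(0, min(H, s + L + 12) − (s + L))

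**Results for L = 24**

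| H | s | LC ends | LC time covered | Post-LC months observed | Maintenance year ends |
|---|---|---|---|---|---|
| 15 | 0 | 24 | 15/24 = 62.5% | 0 of 12 | 36 |
| 15 | 3 | 27 | 12/24 = 50% | 0 of 12 | 39 |
| 12 | 0 | 24 | 12/24 = 50% | 0 of 12 | 36 |
| 12 | 3 | 27 | 9/24 = 37.5% | 0 of 12 | 39 |

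In all four cases no post-LC cohort can be counted in either arm. The denominator E_LC − E_PO has nothing to observe, and C_LC / (E_LC − E_PO) is undefined within the horizon.

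**Third cohort.** If 12-month cohorts run back to back from month 3 (an assumption), they start at months 3, 15 and 27. The third starts outside the window.

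**Sensitivity, L = 12.** With H = 15 and s = 0, the LC ends at month 12 and 15 − 12 = 3 of 12 post-LC months are observed. With s = 3, the LC ends at month 15 and none are. With H = 12, none are observed for either start.

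**Window needed.** 24 + 12 = 36 months, or 3 + 24 + 12 = 39 months: 21 to 24 months past month 15. LC costs need logging only to the end of the LC, at month 24 or 27, which is 9 to 12 months past month 15.

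**Discounting.** At an assumed 3% a year, the factors are 1/1.03² = 0.943 and 1/1.03³ = 0.915. They are relevant only if the window is extended.

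**The case against.** The strongest reply is that the 24-month LC is itself one side of the contradiction. The Abstract and the Overview say 12 months, Table 2 also lists a maintenance survey or checklist at 12 months, and the 2 years in the BHF-LC section span action periods as well as sessions. This is fair, and it is why reconciling the durations comes first. It does not rescue the ratio: even a 12-month LC leaves at most 3 of 12 post-LC months in view, and the 12-month survey is not the Table 1 outcome.

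Cohorts might also overlap. No section says they run in sequence, so a third could start before month 15. Under a 2-year LC, however, it would precede LC completion and fail the definitions in Table 2 and Effect measurement.

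A reader might infer four stronger things that the article does not support:
- **That the maintenance count can never be obtained.** It can be taken later, and Table 2 plans it. The defect is the stated horizon and the mismatch with costs cut at month 15.
- **That every other LC ratio is understated.** Reach work comes early. Counts of cohorts initiated are cut by the same window as their costs, so the direction of any bias is unknown. LC spending after month 15 cannot affect the first cohort's 12-month BMI z-score.
- **That 37.5% or 50% of LC cost is lost.** These are shares of time, and the late-stage label in Table 2 carries no month.
- **That the 6-month BMI z-score ratio uses costs incurred after 6 months.** Data analysis does not say so.

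The case for not discounting is acceptable at 15 months. The article also calls this a pilot and expects low power for sustainability, but low power does not excuse a ratio that the stated window cannot yield.

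**Conclusion.** The point holds for the maintenance analysis. The 12-month, 15-month and 2-year statements are incompatible, and under the stated 2-year LC none of the 12 post-LC months falls inside the horizon, whichever start month is assumed. The maintenance ICER cannot be produced as defined within that horizon. A count taken later would be set against LC costs from a shorter window, probably missing part of the late-stage planning cost. The 15-month window covers 62.5% or 50% of LC time, depending on the unstated start month.

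The zero rests on the 24-month LC and on the post-LC definition of maintenance, both stated in the article. The size of the missing cost cannot be derived from it. This should be corrected before analysis, because the plan's own horizon defeats one of its own ratios for an outcome in the primary aim. The conclusion does not extend to the other ratios.

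**What to change.** 1. Reconcile the 12-month, 15-month and 2-year statements in the Abstract, the Overview of economic evaluation and the BHF-LC section, and state the month in which the LC starts.
2. Keep 15 months for the first-cohort outcomes.
3. For maintenance, state one matched window for cost and outcome covering the full LC and the year after it (to month 36 or 39). Use the count already planned in Table 2, taken in both arms over the same calendar period, and continue the LC time logs to the end of the LC.
4. Revisit the no-discounting rationale for this analysis only, for example an assumed 3% with 0% as sensitivity.
5. If the longer window is not feasible, drop the maintenance ICER and report sustainability-planning cost alone.

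**Cost.** Items 1, 2, 4 and 5 are wording. Item 3 adds about 9 to 12 months of LC time logging, a real burden given that Challenges and limitations already expects incomplete logs. Table 1 enters no package-only cost for this ratio, so that arm needs no extra logging for it. It does need a cohort count beyond the baseline, 6- and 12-month data that its memorandum of agreement covers.

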### Effect measurement

The outcomes measured across implementation strategies and BHF intervention are described in Table 1. At the community level, the outcome associated with the fund and contract dissemination strategy is BHF program adoption, defined as (1) an objective count of communities responding to call for LOI and full application and (2) an objective count of communities responding to RFA and contracted to implement BHF. In addition, the BHF Online Training Resources and Program Package strategy targets outcomes of adoption, measured as an objective count of numbers of BHF cohorts initiated, and implementation, operationalized as community facilitator competence using the knowledge check score obtained from the BHF online training resource and direct observation of implementation fidelity (i.e., adherence to protocol, engagement, and dose [i.e., the number and duration of sessions conducted per cohort]). Finally, the LC implementation strategy involves outcomes of (1) reach, measured as the number, proportion, and representativeness of eligible family screened; (2) adoption, measured as an objective count of BHF cohorts initiated; (3) implementation fidelity, measured using the fidelity checklist via direct observation conducted by the trained research staff; and (4) sustainability, operationalized as an objective count of BHF cohort continued following the completion of LC sessions.

At the individual level, the effectiveness outcome will be assessed using a matched cohort design to determine changes in BMI *z*-scores from baseline to 6 and 12 months among BHF intervention participants across BHF-LC and BHF-PO conditions. We will apply an intention-to-treat approach when conducting the economic evaluation of the BHF intervention (effectiveness as the outcome measure).

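### Discounting is waived because the duration is short, but the Maintenance ratio spans about 36 months and does not fit the stated 15-month horizon

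*Protocol article*

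**What the plan says.** The discounting rule is in the Overview of economic evaluation: "Costs and benefits will not be discounted due to a short duration". It covers every cost and every benefit, and gives no other reason.

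The same paragraph sets the duration it relies on. "The time horizon of the within-trial CEA will be across a 15-month period of time", split into "first 3 months for preparation, and later 12 months for BHF intervention" and chosen to allow time "to complete the whole implementation process of one BHF cohort". Earlier in that section the LC is to be evaluated for, among other outcomes, "sustainability for the duration of the trial (12 months").

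Other sections describe longer periods:

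- The section on the BHF Action Learning Collaborative describes "collaborative learning sessions followed by action periods over a 2-year implementation period".
- Table 2 (under Study design), LC Maintenance row, defines the outcome as "Objective count of sustained implementation of cohorts in the year following completion of the LC intervention". The same cell also lists a survey or checklist at 12 months.
- Effect measurement repeats the post-LC definition: "an objective count of BHF cohort continued following the completion of LC sessions".
- Table 1 divides LC training and consultation cost by the BHF-LC minus BHF-PO difference in continued cohorts, and reads the result as a cost per additional third cohort.

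**The concern.** Discounting is commonly left out when costs and effects fall within about a year. The Maintenance ratio is not of that kind. Its costs accrue during a 2-year LC and its effect is counted afterwards, so the reason given does not cover it. Because costs come before effects, leaving out discounting also moves the ratio in a predictable direction, provided both are discounted at the same rate.

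Stating costs in 2022 US dollars does not fill the gap, since it adjusts for price level and not for time preference.

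Behind this lies a larger inconsistency. The 12-month and 15-month periods that make the duration short cannot contain the LC or the year after it. As written, the reader cannot tell which costs and which cohorts enter the Maintenance ratio.

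**Working it through.** **The plan's own figure.** 3 months of preparation + 12 months of intervention = 15 months. The stated horizon adds up.

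**Span of the Maintenance ratio.** 24 months of LC + 12 months of counting = 36 months from LC start, or 39 if the 3 preparation months come first. Adding those 3 months to both costs and effects leaves the multipliers below unchanged. The third cohort in Table 1 points the same way: the article plans 2 cohorts per community, while the 15-month horizon is sized for one.

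**Effect of discounting.** At annual rate r, the mean discount factor for a flow spread evenly from year a to year b is

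D(a,b) = [(1+r)^−a − (1+r)^−b] / [(b−a)·ln(1+r)].

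The discounted ratio is the undiscounted ratio multiplied by D(costs)/D(effects). The undiscounted ratio is too low by 1 − D(effects)/D(costs).

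Assumptions, none given in the documents: rates of 1.5% to 7%; effects spread evenly over years 2–3; LC cost either late (years 1.5–2) or even over years 0–2. The late profile is closer to the plan. Table 2 marks the LC maintenance activities as late, and its footnotes divide cost among outcomes by activity.

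At 3%:
- D(effects) = 0.9288.
- Late costs: D = 0.9496; 0.9496/0.9288 = 1.022.
- Even costs: D = 0.9710; 0.9710/0.9288 = 1.045.

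| Rate | Late costs: multiplier (undiscounted too low by) | Even costs: multiplier (undiscounted too low by) |
|---|---|---|
| 1.5% | 1.011 (1.1%) | 1.023 (2.2%) |
| 3% | 1.022 (2.2%) | 1.045 (4.3%) |
| 5% | 1.037 (3.6%) | 1.076 (7.1%) |
| 7% | 1.052 (4.9%) | 1.107 (9.7%) |

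Moving the effect to the start or the end of the counting year gives a full range at 3% of 1.007 to 1.061.

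**Ratios that stay inside 15 months.** In an extreme case, with costs even over 15 months and all effect at month 15, the 3% multiplier is 0.9818/0.9637 = 1.019.

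**Effect of the horizon conflict.** With LC cost even over 24 months, a 15-month window from LC start captures 15/24 = 62.5% of it and a 12-month window captures 12/24 = 50%. With late costs (months 18–24), neither window captures any. Neither contains any of the year in which sustained cohorts are counted.

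**The case against.** The strongest reply is that the no-discounting sentence agrees with the paragraph it closes: for a 15-month horizon, short duration is an acceptable reason. On this view the fault is the horizon, and discounting alone would not repair it. That is right, and it sets the order of the fix. It does not rescue the sentence for the Maintenance row. If the post-LC count stands, the reason fails; if 15 months governs, the row's effect lies outside the analysis. The 12-month survey or checklist in Table 2 shows that the timing is unsettled, but Table 1 uses the cohort count as the effect.

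A second reply is that the shift is immaterial. The denominator is a difference in cohort counts between four and three communities. For illustration, if that difference were 2, a change of one would move the ratio by +100% (to 1) or −33% (to 3). The article also calls this a pilot evaluation and does not aim at decision makers' use of the results. This stands, and it is why the point has low priority.

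Three stronger readings are tempting, and the documents do not support them:

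- **That the Maintenance ratio is understated without qualification.** The direction requires one common rate for costs and effects. If only costs were discounted, the ratio would fall (multiplier 0.971 at 3% with even costs).
- **That the even-cost figures are the best estimate.** Table 2's timing and activity-based allocation point to the late profile, which gives about half the effect.
- **That Maintenance alone is affected because costs and effects fall close together in every other row.** Table 1 charges the whole of the LC's activities to the Effectiveness row. If those costs run for 2 years while BMI z-score is measured at 6 and 12 months, that row also exceeds 15 months, and part of its cost comes after its effect.

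**Conclusion.** The point holds in a limited form. The short-duration reason does not apply to the Maintenance ratio, which spans about 36 months from LC start against a stated 15. With costs and effects discounted at one rate, the undiscounted ratio is about 2% low at 3% and 4% low at 5% under late costs, or about 4% and 7% low under even costs. Rates, cost profiles and effect timing are assumptions, and nothing in the article shows that a conclusion turns on a shift of this size. The underlying fault is the set of incompatible periods: 12 months, 15 months, 2 years, and the year after the LC. The rule remains reasonable for ratios whose costs and effects do fall within 15 months.

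**What to change.** 1. Reconcile the 12-month, 15-month, 2-year and year-after-LC periods, and state for each Table 1 ratio the window over which its costs and its effects are counted.
2. Limit the no-discounting sentence to ratios whose costs and effects both fall within the 15-month horizon.
3. For any longer ratio (Maintenance, and Effectiveness if all 2-year LC costs enter it), discount costs and effects at one stated annual rate. Vary that rate, including 0%, in the one-way deterministic sensitivity analysis already planned.

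The cost is a few sentences, one factor in the spreadsheet and a little more analysis work. Activity dates are needed, and the planned time tracking should supply most of them. The Maintenance ratio will look slightly less favourable.
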